## Abstract

Plant-based diets (PBDs) emphasise higher intakes of plant foods and lower intakes of animal foods, and they have been associated with reduced cardiovascular morbidity/mortality and lower cardiovascular disease (CVD) risk factors. Evidence is limited regarding the dietary profile, diet quality, and nutritional adequacy of PBDs, including their impact on CVD risk compared with traditional meat-eating diets in Australians. The PBD Study (PBDS) is a cross-sectional study that will recruit 240 adults from the Hunter region (NSW) without known CVD who are habitually consuming vegan (no animal flesh/animal products), lacto-ovo vegetarian (dairy and/or eggs only), pesco-vegetarian (fish/seafood only), or semi-vegetarian (minimal animal flesh) diets or are a regular meat-eater. To investigate dietary profile, diet quality, nutritional adequacy, and CVD risk, questionnaires (medical history, demographics, and physical activity), blood samples (biomarkers), physical measures (anthropometry, blood pressure, body composition, and bone density), and dietary intake (food frequency questionnaire and diet history) will be collected. One-way ANOVA and Kruskal–Wallis tests will compare the CVD risk and other quantitative measures, and Chi-square or Fisher’s Exact tests will be used for qualitative data. Directed acyclic graphs will determine the confounding variables, and linear regression and mediation analyses will account for the confounders and estimate the effect of dietary patterns on CVD risk. *p*-values will be adjusted using the Benjamini–Hochberg method to control the False Discovery Rate to 5%.

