Through the adaptation of dietary categorisations employed in the ‘45 and Up’ study, we have demonstrated that individuals following PBDs had significantly lower body weight, central obesity, and BMI compared with regular meat-eaters in more than 9000 women from the Australian Longitudinal Study of Women’s Health (ALSWH) [12]. Moreover, regular meat-eaters consuming meat daily or multiple times per day had significantly higher body weight, central obesity, and BMI compared with those consuming meat less than daily but at least 2 times per week. Our study demonstrated a dose-dependent association between frequency of weekly meat intake and body weight, central obesity, and BMI, even after adjusting for the confounders [12]. In this same cohort, a significantly lower prevalence of diabetes was reported in vegetarians compared with meat-eaters, and high-quantity meat consumers reported a significantly higher prevalence of impaired glucose tolerance (manuscript under review). The prevalence of individuals following PBDs in both the ‘45 and Up’ study and ALSWH was only ~2%, resulting in the pooling of some data for comparison with regular meat-eaters, which limits specific diet and health comparisons across the PBD continuum. Noteworthy, the ‘45 and Up’ and ALSWH studies collected data from 2006–2014 and 2013, respectively, prior to the surge in global popularity of these diets; therefore, it is crucial that the current dietary profile of the PBD is investigated in Australians.

Only secondary analyses of population-based data form the basis of our current understanding and evidence around PBDs and health in the Australian population, and these findings reflect the PBD climate from 8–16 years ago, prior to the rapid surge in its adoption. Therefore, an Australian study methodologically targeting PBDs is warranted to address the national and global concern, which is the implementation of sustainable dietary patterns for future food ecosystems.

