### 2.7. Sample Size

Based on previous estimates of variance in 10-year CVD risk scores using the Framingham algorithm (Mean = 13.3, SD ± 5.77) [26] to elicit 80% power at a significance level of 0.05 to detect a 25% (Δ = 3.33) difference in CVD risk scores among at least one group following a PBD pattern compared with a regular meat-eating dietary pattern, a sample size of *n* = 240 participants (48 per dietary pattern) is required. Previous observational studies on dietary pattern and lifestyle have reported differences of 27% and 20–22% in Framingham Risk Scores [27,28]. Moreover, we have reported reductions of 13–23% in RCTs following dietary interventions for only 3–4 weeks [29,30]. A longitudinal study which employed a healthy PBD index reported a 47–68% lower risk of developing CVD in individuals among the 2nd and 3rd tertiles of adherence to a healthful PBD compared with their 1st tertile counterparts [31]. Similarly, vegetarians have been shown to have a 22% lower rate of ischaemic heart disease than meat-eaters in the EPIC-Oxford study of more than 48,000 participants followed up after 18 years [32]. Therefore, after review of previous studies’ CVD risk outcomes, the authors arrived at the 25% estimated difference in Framingham Risk Score between at least the two extreme dietary patterns (vegan vs. regular meat-eating diet). This cross-sectional study meets the target sample size of 48 per group to be statistically powered, and estimates are substantially supported by the previous literature. Authors recognise that the modest sample size of 240 may be used as a pilot or ‘proof of concept’ study for larger cohorts in the future.

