### 2.8. Statistical Analyses

All data will be assessed for normality by inspecting visual plots, such as histograms, quantile plots, and Q-Q plots, within each dietary pattern group for each variable. One-way ANOVA or Kruskal–Wallis tests will be used for comparison of CVD risk scores, dietary intake, and cardiometabolic parameters, including all clinical measures, medical/demographics, and blood parameters across dietary pattern groups. Chi-square or Fisher’s Exact tests will be used to compare qualitative dietary intake data and other categorical data across dietary pattern groups. Directed acyclic graphs (DAGs) will be used to display dependencies between outcome (5-year absolute CVD risk and 10-year CVD risk scores), exposure (different categories of dietary patterns determined via classifications presented in Table 1), and confounding/mediating variables to determine the minimum set of variables necessary to control for confounding [33] (Figure 2). Linear regression will be used to account for potential confounding factors described in the DAGs, such as age, sex, alcohol use, smoking status, and physical activity levels. Mediation analysis will be used to estimate the effect of PBDs on CVD risk that is not mediated through BMI [33,34]. Predictably, there will be intrinsic differences between dietary pattern groups, as the study design endeavours to evaluate the true characteristic of each group (chronic diseases, lifestyle choices, etc.). To address this and remove risk of overadjustment, a sensitivity analysis will be performed on potential additional important confounding variables not already identified in the DAGs to assess how robust the results are when comparting the additional confounding factor [35,36]. *p*-values will be adjusted using the Benjamini–Hochberg method to control the False Discovery Rate to 5%.

All statistical analyses will be conducted using StataCorp. 2015. *Stata Statistical Software: Release 14* (College Station, TX, USA: StataCorp LP). Continuous data will be presented as means, SD, median, and interquartile range (25th–75th percentile), and categorical data will be summarised as frequencies and percentages.

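### The sample size is that of a single vegan versus regular meat-eater comparison, but CVD risk is tested with an unordered five-group test, and neither that contrast nor an ordered one is pre-specified

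*Protocol article*

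**What the plan says.** **Sizing (section 2.7).** The inputs are "Mean = 13.3, SD ± 5.77" for the 10-year Framingham score and "80% power at a significance level of 0.05". The target is "to detect a 25% (Δ = 3.33) difference in CVD risk scores among at least one group following a PBD pattern" compared with regular meat-eaters, giving "48 per dietary pattern) is required", or 240 in all. Later in the section the 25% is justified as a "difference in Framingham Risk Score between at least the two extreme dietary patterns (vegan vs. regular meat-eating diet").

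**Testing (Abstract and section 2.8).** The Abstract says "One-way ANOVA and Kruskal–Wallis tests will compare the CVD risk and other quantitative measures", and section 2.8 repeats it: "One-way ANOVA or Kruskal–Wallis tests will be used for comparison of CVD risk scores, dietary intake, and cardiometabolic parameters". Linear regression then adjusts for confounders, with diet described as categories. No pairwise or ordered contrast is named.

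**Order of the diets.** The Introduction calls plant-based diets a continuum and reports from a previous women's cohort: "Our study demonstrated a dose-dependent association between frequency of weekly meat intake and body weight, central obesity, and BMI". The only dose–response analysis in the plan (section 2.5) is optional and concerns years on the diet, not the amount of animal food eaten.

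**The concern.** The comparison that sets the sample size is not the comparison that is tested. One-way ANOVA and Kruskal–Wallis spread the test over four degrees of freedom and give the same p-value however the five groups are labelled. If the middle diets fall between vegan and regular meat-eating, a 3.33-point gap between the extremes is diluted across all five groups, and power drops below the stated 80%. A difference the study was meant to find could then be missed. A significant omnibus result would not by itself show that the sized pair differs, or that risk rises along the spectrum. If contrasts are first chosen after the group means are seen, their p-values are hard to defend.

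**Working it through.** **Inputs from section 2.7:** SD 5.77, Δ = 3.33 (25% of 13.3), alpha 0.05, power 80%, n = 48 in each of k = 5 groups. Sidedness is not stated; two-sided reproduces the plan's figure.

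**Step 1: reproduce the plan's figure.** For two means,
n = 2 × (1.960 + 0.842)² × 5.77² / 3.33² = 47.1, so 48 per group.
This matches. A one-sided test would give 38. The stated size is therefore that of one unadjusted pairwise comparison. Using the pooled SD from all five groups (235 df), the noncentrality is 3.33 / (5.77 × √(2/48)) = 2.83 and power is 80.4%.

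**Step 2: omnibus test.** Noncentral F with 4 and 235 df and λ = 48 × Σ(μᵢ − μ̄)² / 5.77². For equal steps, Σ(μᵢ − μ̄)² = 0.625 × 3.33² = 6.93, so λ = 48 × 6.93 / 33.29 = 9.99 and power is 70.6%. Kruskal–Wallis, simulated on normal data (4,000 runs), gives about 68%.

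**Step 3: linear trend.** Contrast (−2, −1, 0, 1, 2), noncentrality Σcᵢμᵢ / (5.77 × √(10/48)). For equal steps this is (2.5 × 3.33) / 2.634 = 3.16 and power is 88.3%.

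**Step 4: other shapes.** The shapes are assumptions. Means are multiples of 3.33, in the order vegan, lacto-ovo, two intermediate groups (pesco- and semi-vegetarian), regular meat-eater.

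| Shape | ANOVA | Linear trend | Vegan vs meat-eater |
|---|---|---|---|
| Equal steps (0, ¼, ½, ¾, 1) | 70.6% | 88.3% | 80.4% |
| Middle three at the midpoint (0, ½, ½, ½, 1) | 59.4% | 71.2% | 80.4% |
| Vegan and lacto-ovo low (0, 0, ½, ½, 1) | 76.1% | 88.3% | 80.4% |
| In proportion to 0, 0, 1, 2, 7 servings | 75.7% | 82.1% | 80.4% |
| Two low, three high (0, 0, 1, 1, 1) | 95.3% | 96.5% | 80.4% |
| One extreme group alone differs | 82.2% | 71.2% | 80.4% |
| One middle group alone differs (0, 0, 1, 0, 0) | 82.2% | 5% | 5% |

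With equal steps but the two intermediate groups scored in the wrong order, the trend test still has 80.9%.

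**Step 5: size needed for 80% with equal steps.** ANOVA needs 59 per group (295 in all); the trend test needs 39 per group (195 in all).

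All figures are unadjusted. The residual SD after confounder adjustment is not given, and the planned Benjamini–Hochberg adjustment may lower power further.

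**The case against.** The strongest reply is that an unordered test suits the formal alternative in section 2.7, a difference in at least one plant-based group, and that the protocol states no ordered hypothesis for CVD risk. A reader might infer from the continuum wording and the dose-dependent finding that the authors expect risk to rise step by step and then fail to test it. The document does not go that far. That finding concerns body weight, central obesity and BMI, not risk scores, and BMI is not among the inputs listed for the chosen Framingham equation (section 2.4). The continuum remark complains about pooling, which argues for keeping categories apart. BMI is drawn as a mediator between diet and CVD risk (Figure 2 caption), so a graded risk is plausible, but it remains an inference.

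The groups also lack a clean order. In Table 2 vegan and lacto-ovo both total 0 flesh servings, semi-vegetarian is at most 2, and pesco-vegetarian is at least 1 with no upper limit and seafood only. The Abstract lists pesco before semi; Table 2 does the reverse. Declining to assume an order is defensible, and the last two rows of the table show what a wrong assumption costs. This part of the objection stands, and it is why a trend test can only be an addition.

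It is also fair that the plan does not rest on the omnibus p-value alone. Group summaries will be presented, the adjusted regression can yield the vegan versus meat-eater difference, and contrast details are often left to a SAP. But this document itself fixes both the sizing and the group test, and they do not match. Whether or not a gradient exists, the contrast that justifies the 25% should be named.

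**Conclusion.** The point holds as a mismatch between sizing and testing. The 48 per group reproduces only as a single two-group comparison, justified on vegan versus regular meat-eater, while the named test for CVD risk is an unordered 4-df omnibus test. In four of the five shapes tried with vegan lowest and no reversal before regular meat-eater, leaving aside those in which one group alone differs, ANOVA has 59–76% power, below the stated 80%. The sized contrast has 80.4% and the trend 71–88%. The fifth, with three groups sharing the higher mean, gives ANOVA 95%.

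These figures rest on the plan's SD, equal groups of 48, an unadjusted alpha of 0.05 and assumed shapes. They do not show that the omnibus test is wrong, nor that the authors predicted a CVD-risk gradient. If a single group stands apart, ANOVA has 82% and is the better test than the trend. This is a worthwhile and inexpensive improvement, not a flaw that invalidates the design.

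**What to change.** - Keep the one-way ANOVA or Kruskal–Wallis comparison.
- Pre-specify, in the confounder-adjusted regression, the vegan versus regular meat-eater contrast on which section 2.7 justifies the 25%.
- Add, as a supplementary analysis for the two risk scores, a 1-df trend across vegan, lacto-ovo, pesco-vegetarian, semi-vegetarian and regular meat-eater, stating that this order is an assumption. Check it with weekly flesh frequency from the Australian Eating Survey as a continuous exposure in the same model.

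The cost is a few sentences and a few more lines of output, from data the study already plans to collect. The downsides should be stated with it:

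- A few more p-values enter the false-discovery family.
- The order of pesco- and semi-vegetarian is debatable.
- The continuous check is lumpy, since two groups of 48 (96 of 240 participants) have zero flesh intake by definition.
- The trend has less power than ANOVA if one group alone differs (71% against 82% for an extreme group, about 5% against 82% for a middle group), so it must not replace the group comparison.

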## 1. Introduction

Plant-based diets (PBDs) focus on high intakes of plants/plant-based foods and low intake of animal flesh/animal-based products and have been gaining traction worldwide. The global movement towards a PBD has several drivers, such as ethical concerns [1], reduced environmental impact and improved sustainability of the food system [2,3,4], concerns for animal welfare [1], and perceived healthiness [1,5]. A recent systematic review and meta-analysis of 12 prospective cohort studies, which included more than 508,000 participants, reported an inverse association between PBDs and risk of all-cause mortality and coronary heart disease mortality [6]. Moreover, another meta-analysis of 18 cross-sectional and 10 prospective cohort studies demonstrated that adherence to vegetarian/vegan dietary patterns compared with omnivorous dietary patterns was associated with lower BMI, blood cholesterol, LDL-cholesterol, and glucose concentrations. A significantly lower risk of ischaemic heart disease and total cancer mortality was also evident in the vegetarian/vegan dietary patterns [7]. PBD indexes have enabled investigation into the degree of adherence to and quality of PBDs and their subsequent health outcomes, with healthy PBDs that are rich in wholegrains, fruits, vegetables, legumes, nuts, tea, and coffee and low in animal foods being associated with lower risk of cardiovascular disease (CVD) mortality and all-cause mortality [8]. Conversely, unhealthy PBDs are characterised by having a higher intake of total energy and energy from carbohydrates and a lower intake of fruits, vegetables, and, thus, lower fibre and micronutrient intake [8]. Individuals following these dietary patterns have been shown to be more likely to drink higher amounts of alcohol, be less physically active and obese, and have hypertension [8].

Despite the promising findings of the aforementioned literature, the majority of evidence around PBDs and their impact on health outcomes are reported in populations from USA and Europe [6,9], with only one cohort study to date conducted in Asia and one in Australia [10]. Market research has demonstrated that the adoption of vegetarian-style dietary patterns by Australians is rising from 1.7 million in 2012, to 2.2 million in 2014, and to 2.5 million in 2018 (more than 12% of the total population) [11]. Despite the growing popularity of PBDs among Australians, limited evidence exists around the dietary profile, nutritional adequacy, and chronic disease risk specific to the Australian population. The lack of standardised definitions and classification of PBDs has also been acknowledged [6] and requires refinement to examine and compare adequately the dietary intake, nutritional concerns, and health outcomes across the spectrum of PBDs compared with traditional meat-eating diets.

Secondary analysis of the ‘45 and Up’ study by the Sax Institute is the only cohort study to investigate the effect of vegetarian diets (including various categories of vegetarian diets) and all-cause mortality in Australians and, converse to studies conducted in other countries, found there to be no evidence that following a vegetarian style dietary pattern has an independent protective effect on all-cause mortality [10]. Although the longitudinal cohort study was large (*n* = 243,096), rigorously designed, and extensively controlled for confounders, several limitations pertain to the sole reliance on it for informing the PBD climate among Australians; these are (1) the study primarily aimed to investigate a wide range of exposures and outcomes of public health importance for the ageing population; (2) a 24 h recall or FFQ was not employed; thus, diet was examined only through brief dietary behaviour questions in the baseline questionnaire; (3) limited PBDs were examined, as researchers could not distinguish between vegans and lacto-ovo vegetarians; and (4) the study was conducted between 2006 and 2014. The ‘45 and Up’ study provides historical insight into vegetarian-style diets and their association with disease, but, moreover, it initiates the need for an Australian-population cohort study designed primarily to examine the current association between PBDs and human health.

Through the adaptation of dietary categorisations employed in the ‘45 and Up’ study, we have demonstrated that individuals following PBDs had significantly lower body weight, central obesity, and BMI compared with regular meat-eaters in more than 9000 women from the Australian Longitudinal Study of Women’s Health (ALSWH) [12]. Moreover, regular meat-eaters consuming meat daily or multiple times per day had significantly higher body weight, central obesity, and BMI compared with those consuming meat less than daily but at least 2 times per week. Our study demonstrated a dose-dependent association between frequency of weekly meat intake and body weight, central obesity, and BMI, even after adjusting for the confounders [12]. In this same cohort, a significantly lower prevalence of diabetes was reported in vegetarians compared with meat-eaters, and high-quantity meat consumers reported a significantly higher prevalence of impaired glucose tolerance (manuscript under review). The prevalence of individuals following PBDs in both the ‘45 and Up’ study and ALSWH was only ~2%, resulting in the pooling of some data for comparison with regular meat-eaters, which limits specific diet and health comparisons across the PBD continuum. Noteworthy, the ‘45 and Up’ and ALSWH studies collected data from 2006–2014 and 2013, respectively, prior to the surge in global popularity of these diets; therefore, it is crucial that the current dietary profile of the PBD is investigated in Australians.

Only secondary analyses of population-based data form the basis of our current understanding and evidence around PBDs and health in the Australian population, and these findings reflect the PBD climate from 8–16 years ago, prior to the rapid surge in its adoption. Therefore, an Australian study methodologically targeting PBDs is warranted to address the national and global concern, which is the implementation of sustainable dietary patterns for future food ecosystems.

This Australian-first population-based study to examine the dietary profile, health status, and CVD risk of individuals following various PBDs will be titled the Plant-Based Diet Study (PBDS). This study will be strengthened by the purposeful recruitment methodology guided by specific strict dietary criterion to capture true habits of dietary patterns, which is not logistically and financially feasible to examine via a randomized controlled trial. Outcomes of this study will provide a database for studying PBDs, aid in the design of future longitudinal studies, and inform current Australian dietary guidelines, which are lagging regarding guidance towards sustainable dietary patterns.

## 2. Materials and Methods

### 2.1. Study Design and Setting

The PBDS is a cross-sectional study conducted at the Nutraceuticals Research Program, School of Biomedical Sciences & Pharmacy, University of Newcastle, Callaghan NSW, Australia. Eligible participants (Table 1) will be invited for one timepoint of data collection to examine the dietary profile, diet quality, nutritional status, and risk of developing CVD in adults consuming various PBDs and regular meat-eating diets (RMDs). To enhance representativeness of the Australian adult population and to gain a true understanding of the characteristics of the dietary patterns of interest, every effort will be made to invite all eligible individuals to participate in the study, including those with chronic health conditions.

**Table 1 nutrients-15-02850-t001:** Inclusion and exclusion criteria for the PBDS.

Inclusion Criteria	Exclusion Criteria
Adults ages 35–75 years.	Ages <35 and >75 years.
No history of CVD, such as myocardial infarction, coronary insufficiency, angina, ischaemic stroke, transient ischaemic attack, haemorrhagic stroke, peripheral artery disease, heart failure, or pacemaker implant.	Receiving treatment for CVDs.
Consuming one of the following dietary patterns in Table 2 for at least 6 months; (1) vegan, (2) lacto-ovo vegetarian, (3) semi-vegetarian, (4) pesco-vegetarian, and (5) regular meat-eaters.	Made significant changes to their dietary pattern, food choices, lifestyle and/or physical activity levels in the past 6 months (determined by an Accredited Practising Dietitian) and/or practicing in (or in the last 30 days) another research trial involving dietary and/or physical activity intervention.
	Pregnant/lactating.

